### **5.5 Withdrawal of individual subjects**

The participants can withdraw from the SMILE registry at any time and are not required to provide a reason for discontinuing their participation. The data collected up to that point will be used for the research.

### **5.6 Premature termination of the study**

Participants may withdraw from the study at any time, either at their request or if the MUMC, the governing authorities, or the ethics review committee decides to terminate the study.

### **5.7 Feasibility of the recruitment schedule**

The recruitment for the SMILE registry is designed to be feasible and efficient within the clinical workflow. Patients with moderate-severe MR are identified during routine echocardiographic examinations. These patients are subsequently contacted via post or telephone to inform them about the registry and their eligibility to participate. The use of an opt-out/no-objection system ensures that recruitment can proceed without the need for formal written consent, reducing delays and enabling the inclusion of nearly all eligible patients. This approach allows for a comprehensive and representative dataset while respecting patient autonomy and privacy.

## **6 Safety**

### **6.1 Temporal halt for reasons of subject safety**

As no additional procedures are performed for the study and standard care is followed, there are no risks associated with participation, and therefore, a safety halt is not applicable.

### **6.2 Safety monitoring**

As the study involves only standard care without additional interventions, comprehensive safety monitoring or the establishment of a Data Safety Monitoring Board (DSMB) is not deemed necessary; however, Clinical Trial Center Maastricht (CTCM) manages the Castor database to ensure proper data handling and regulatory compliance.

### **6.3 (Serious) Adverse events and suspected, unexpected severe adverse reactions**

This study follows standard clinical care procedures, and no additional interventions are introduced. Therefore, no specific adverse events or suspected, unexpected severe adverse reactions related to the study are expected. Any adverse event will be considered part of the standard course of care and will be documented in the patient's medical records as per routine clinical practice. These events will not be specifically attributed to the study, and no additional reporting beyond standard care requirements is deemed necessary.

### **6.4 Annual safety report**

Since this study involves only standard care without additional interventions, there are no study-related risks or adverse events to report. Consequently, the preparation of an annual safety report is not applicable.

### **6.5 Data monitoring safety board**

As the study involves only standard care without additional interventions, comprehensive safety monitoring or the establishment of a DSMB is not deemed necessary; however, CTCM manages the Castor database to ensure proper data handling and regulatory compliance.

## 7 Statistical analyses

### 7.1 Baseline, primary, secondary outcomes

Analysis will begin with descriptive statistics to summarise baseline characteristics. Categorical variables will be presented as counts and percentages and compared using the Chi-square test. Ordinal variables will be reported as frequencies and compared using ordinal or non-parametric tests. Continuous variables will be presented as means ( $\pm$  standard deviations) or medians (interquartile ranges), depending on the distribution, and compared using the independent t-test for normally distributed data or the Mann–Whitney U test for non-normally distributed data.

Time-to-event outcomes, including all-cause mortality and time-to-first heart failure hospitalisation, will be analysed using Kaplan–Meier estimates and compared using the log-rank test. Associations between baseline characteristics and clinical outcomes will be evaluated using multivariable Cox proportional hazards regression models, with results presented as hazard ratios (HRs) and 95% confidence intervals (CIs). A minimum of 10 events per variable will be considered to ensure statistical robustness.

Longitudinal changes in echocardiographic parameters and HRQoL will be analysed using mixed-effects models to account for repeated measurements within patients. MR severity will be demonstrated as an ordinal outcome, while continuous echocardiographic measures and HRQoL outcomes will be analysed using linear mixed-effects models. Treatment success will be evaluated using responder-based analyses based on annual follow-up assessments, and predictors of treatment success will be analysed using multivariable logistic regression models, with results presented as odds ratios (ORs) and 95% CIs. Analyses will be stratified by MR aetiology and, where appropriate, by management strategy (conservative, catheter-based, or surgical). Missing data will not be imputed; primary analyses will be conducted using all available data, with sensitivity analyses performed in complete-case cohorts. Statistical significance will be set as a two-sided  $p$ -value  $< 0.05$ .

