## **1 Introduction and rationale**

Mitral regurgitation (MR) affects more than 10% of individuals aged 75 years and older and is associated with adverse cardiovascular outcomes, including heart failure, increased hospitalizations, and mortality (1-3). Despite its prevalence, MR is often undertreated, leading to progressive disease, adverse cardiac remodelling, and diminished quality of life (HRQoL) (1, 4, 5). While advancements in diagnostic and therapeutic technologies have improved outcomes, optimal management strategies, particularly in asymptomatic patients, remain unclear due to discrepancies in guidelines and a lack of robust data (6-8). However, timely intervention has been shown to improve outcomes significantly (6).

The multicentre prospective Significant Mitral Insufficiency Limburg Evaluation (SMILE) registry aims to evaluate long-term outcomes in patients with moderate-severe MR in routine clinical practice, and to determine clinical and echocardiographic predictors of MR progression and treatment success. Through a multidisciplinary approach, the registry aims to align the progression of mitral valve disease and care pathways with individual patient needs, optimize treatment strategies, and enhance long-term outcomes, including survival and HRQoL.

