## **2 Objectives**

### **2.1 Primary objective**

To evaluate the co-primary clinical endpoints during a five-year follow-up:

- all-cause mortality
- heart failure hospitalisations

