### **4.2 Inclusion Criteria**

All patients aged 18 years and older with moderate-severe MR as determined by echocardiography.

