## **11 Endpoint definitions**

### **11.1 Clinical endpoints (Primary)**

The primary clinical endpoints are all-cause mortality and time-to-first heart failure hospitalisation during long-term follow-up. Mortality and hospitalisation events will be collected during annual follow-up and, when applicable, verified through medical records with corresponding dates recorded.

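### Kaplan–Meier for the co-primary first heart failure hospitalisation in effect censors deaths, so the five-year hospitalisation risk read from it is too high

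*Protocol*

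**What the plan says.** Protocol section 2.1 sets the primary objective: "To evaluate the co-primary clinical endpoints during a five-year follow-up". It then lists all-cause mortality and heart failure hospitalisations as two items. Section 11.1 confirms that they are separate endpoints: "The primary clinical endpoints are all-cause mortality and time-to-first heart failure hospitalisation during long-term follow-up". No composite of the two is defined.

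Section 7.1 gives both endpoints the same treatment. For the second, it says "time-to-first heart failure hospitalisation, will be analysed using Kaplan–Meier estimates and compared using the log-rank test". Associations with baseline characteristics are to be "evaluated using multivariable Cox proportional hazards regression models, with results presented as hazard ratios (HRs) and 95% confidence intervals (CIs"). The same section stratifies analyses by MR aetiology and, where appropriate, by conservative, catheter-based or surgical management.

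The protocol does not mention competing risks or cumulative incidence, and it does not say how a death before a first hospitalisation is handled. It gives no mortality rate, hospitalisation rate or age distribution for the registry.

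**The concern.** A patient who dies without a heart failure hospitalisation can never have one. Death is therefore a competing event for this endpoint and differs from loss to follow-up. Kaplan–Meier offers no place for such a patient except the censored group, and it then assumes that censored patients would have gone on to be hospitalised at the same rate as those still at risk. One minus Kaplan–Meier thus describes a hypothetical population in which nobody dies before hospitalisation. It does not give the share of registry patients who are actually hospitalised within five years.

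This is a single-cohort registry without randomisation, and its primary objective is to evaluate these endpoints over five years. The absolute five-year risk is a natural result to report, and it would be biased upwards. If mortality differs between the planned strata, the size of the bias differs too, so the curves could misstate the difference in hospitalisation risk. The estimator is named in the protocol, so an analysis plan that follows section 7.1 would inherit the problem.

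**Working it through.** **Inputs.** From the protocol: a five-year horizon (section 2.1), separate endpoints (sections 2.1 and 11.1), and Kaplan–Meier for both (section 7.1). The protocol states no figure that could be reproduced and no event rates, so every rate below is an assumption.

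**Notation.** Let *h* be the hazard of first heart failure hospitalisation and *d* the hazard of death without prior hospitalisation, both constant per year, with T = 5 years.

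- Kaplan–Meier with death censored tends to 1 − exp(−5h).
- The actual cumulative incidence is h/(h+d) × [1 − exp(−5(h+d))].

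**One case in full, h = 0.08 and d = 0.10.**

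- 1 − KM = 1 − exp(−0.40) = 33.0%.
- Cumulative incidence = 0.08/0.18 × [1 − exp(−0.90)] = 0.4444 × 0.5934 = 26.4%.
- Excess = 6.6 points, ratio 1.25.

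**Range.** Each cell shows 1 − KM, then cumulative incidence, then the excess in points and the ratio.

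| d per year | h = 0.05 | h = 0.08 | h = 0.12 |
|---|---|---|---|
| 0.02 | 22.1%, 21.1%; 1.0 (1.05) | 33.0%, 31.5%; 1.5 (1.05) | 45.1%, 43.1%; 2.0 (1.05) |
| 0.06 | 22.1%, 19.2%; 2.9 (1.15) | 33.0%, 28.8%; 4.2 (1.15) | 45.1%, 39.6%; 5.6 (1.14) |
| 0.10 | 22.1%, 17.6%; 4.5 (1.26) | 33.0%, 26.4%; 6.6 (1.25) | 45.1%, 36.4%; 8.7 (1.24) |
| 0.14 | 22.1%, 16.1%; 6.0 (1.37) | 33.0%, 24.3%; 8.7 (1.36) | 45.1%, 33.6%; 11.5 (1.34) |

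Excesses were computed before rounding. At d = 0.01 the excess is only 0.5 to 1.0 points (ratio about 1.02).

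**Simulation check.** With 200,000 simulated patients, a five-year hospitalisation risk of 30% in the absence of death, and competing mortality of 20%, 40% and 50%, the product-limit estimates were 30.0%, 29.9% and 29.9%. The Aalen–Johansen estimates were 27.1%, 23.8% and 22.0%, each equal to the observed proportion hospitalised.

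**Effect on strata.** Suppose two strata share h = 0.08 but have d = 0.04 and d = 0.14. Kaplan–Meier tends to 33.0% in both. The actual incidences are 30.1% and 24.3%, so a difference of 5.8 points in realised hospitalisation does not appear.

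**Which deaths count.** The formula needs deaths without prior hospitalisation, which is not the same as all deaths. Hold total five-year mortality at 1 − exp(−0.50) = 39% with h = 0.08. If the death hazard doubles after hospitalisation, the excess is 5.8 points (ratio 1.21). If it triples, the competing hazard is 0.078 per year and the excess is 5.3 points (ratio 1.19). Equating all-cause mortality with competing mortality gives 6.6 points, which is then too large.

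**The case against.** The strongest reply is that little is at stake. The primary objective says the endpoints will be evaluated and does not name an absolute five-year risk as the estimand. Mortality is reported alongside, so a reader sees the competing event. The registry has no power calculation that the bias could upset, and the analysis can be changed later without new data. All of this is fair and bears on consequence. It does not make the Kaplan–Meier curve a correct estimate of hospitalisation risk.

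The protocol also never says that deaths are censored. That is an inference from the method, but a firm one, because ordinary Kaplan–Meier on a non-composite endpoint has no other way to treat them.

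A reader might infer three stronger things that the documents do not support.

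- **That log-rank and Cox are also wrong for hospitalisation.** They are not. With death censored, both address the cause-specific hazard, which is a legitimate target for the secondary objective on associations with baseline characteristics. Gray's test answers a different question: a stratum with many early deaths can look better on hospitalisation simply because its patients died. Replacing log-rank is a choice and not a correction.
- **That this is an elderly, high-mortality cohort, so the bias must be large.** The introduction says MR "affects more than 10% of individuals aged 75 years and older and is associated with adverse cardiovascular outcomes", which concerns prevalence in the population. Eligibility is "All patients aged 18 years and older with moderate-severe MR as determined by echocardiography", and no mortality rate is given.
- **That particular strata, such as conservatively managed patients or those with secondary MR, are the ones distorted.** The protocol does not say that they die more often. The distortion is conditional on mortality differing between strata.

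**Conclusion.** The point holds for the absolute-risk estimator. As written, section 7.1 yields a five-year hospitalisation risk that is too high whenever some patients die first and others are hospitalised later. The direction is certain, but the size cannot be computed from the protocol. Over the assumed grid (h from 0.05 to 0.12 and d from 0.02 to 0.14 per year, constant hazards) the excess runs from about 1 to 11.5 points, ratio about 1.05 to 1.37. At lower competing mortality it becomes negligible. Distortion between strata is possible but depends on a mortality difference that the protocol does not document. The log-rank test and the Cox hazard ratios stand, provided they are read as cause-specific.

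**What to change.** In section 7.1:

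- Keep Kaplan–Meier for all-cause mortality.
- For first heart failure hospitalisation, report the Aalen–Johansen cumulative incidence with death as a competing event, overall and by each planned stratum.
- Log-rank and Cox may stay for hospitalisation. Label them cause-specific and report them beside the cause-specific results for death without hospitalisation.
- Optional: Gray's test where cumulative incidences themselves are compared, and the composite of death or first hospitalisation as a supportive analysis, for which Kaplan–Meier is appropriate.

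The cost is two or three sentences and a little more analysis in standard software. No new data are needed, since sections 5.1 and 11.1 already provide for recording event dates. The one visible consequence is a lower reported hospitalisation risk than Kaplan–Meier would give.

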### **5.2 Randomisation, blinding and treatment allocation**

There is no randomization involved. Participants will continue to receive standard care, and no additional interventions or investigations will be applied.

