### **5.3 Study procedures**

The database does not require any changes to the participants' usual care, and they will not undergo any procedures other than echocardiographic evaluation and follow-up. Follow-up will take place through regular outpatient visits at the referring hospital. Participating patients will be asked to complete an annual SF-36 questionnaire, with follow-up occurring once yearly for five years. Completing the SF-36 questionnaire will take approximately 15 minutes. Additionally, data from patient records will be collected for five years.

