### **5.4 Schedule of assessment**

No additional procedures are planned. All assessments will follow the standard care protocol.

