### **8.2 Recruitment and consent**

The SMILE registry operates under a no-objection system. Patients are eligible for inclusion when moderate-severe MR is observed on a cardiac echocardiogram. These eligible patients are informed about the study through communication via post or telephone, and they are provided with detailed information regarding the purpose and scope of the registry. Patients are explicitly allowed to object to the use of their data. If no objection is raised, their data will be included in the registry. This method ensures compliance with ethical principles while facilitating a comprehensive and unbiased collection of data necessary to evaluate and improve the quality of care for MR patients.

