### **11.2 Disease-specific endpoints (Secondary)**

MR disease progression will be assessed using longitudinal echocardiographic evaluations performed during routine clinical care. MR severity will be assessed according to guideline-recommended criteria at the time of analysis. MR progression will be defined as an increase of at least one MR grade compared with baseline.

In addition, left ventricular (LV) and left atrial (LA) remodelling will be assessed longitudinally using echocardiographic parameters. LV remodelling will be evaluated using LV end-diastolic diameter (LVEDD) and left ventricular ejection fraction (LVEF), while LA remodelling will be evaluated using LA volume index (LAVi). For clinical interpretability, remodelling severity will additionally be categorised based on guideline-recommended cut-off values at the time of assessment. For patients already in the most severe category at baseline, progression will be defined as a relative change of  $\geq 10\%$  from baseline.

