|                                                                    | Aetiology                                 | Categorical | Primary, Secondary                                                         |
|                                                                    | Flail leaflet                             | Categorical | Yes, no                                                                    |
|                                                                    | Involved segment in mitral valve prolapse | Categorical | P1, P2, P3, A1, A2, A3, Posteromedial commissure, Anterolateral commissure |

|                            |                               |             |                                                                                                |
|----------------------------|-------------------------------|-------------|------------------------------------------------------------------------------------------------|
|                            | Severity of MI                | Categorical | Mild (Grade I), Mild to moderate (Grade II), Moderate to severe (Grade III), Severe (Grade IV) |
|                            | ERO                           | Numeric     | Effective regurgitant orifice                                                                  |
|                            | LAVi                          | Numeric     | Left atrial volume index                                                                       |
|                            | Regurgitant volume            | Numeric     | Volume of regurgitation                                                                        |
|                            | E/A ratio                     | Numeric     | Ratio of E-wave to A-wave                                                                      |
|                            | Maximum E-wave velocity       | Numeric     | Maximum velocity of E-wave                                                                     |
|                            | Vena contracta                | Numeric     | Diameter of vena contracta                                                                     |
|                            | PISA radius                   | Numeric     | Proximal Isovelocity Surface Area                                                              |

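### Entry rests on one echo that is probably also the baseline, so change in the MR-severity measures from baseline includes regression to the mean and understates progression

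*Protocol*

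**What the plan says.** On entry, section 8.2 of the protocol states: "Patients are eligible for inclusion when moderate-severe MR is observed on a cardiac echocardiogram". Section 5.7 says how patients are found: "Patients with moderate-severe MR are identified during routine echocardiographic examinations". No confirmatory reading is required.

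On extra examinations, section 5.2 says that "no additional interventions or investigations will be applied", and section 5.4 reads: "No additional procedures are planned. All assessments will follow the standard care protocol". Section 10 adds that the data come from routine clinical evaluation. Section 5.3 is looser: participants are told that "they will not undergo any procedures other than echocardiographic evaluation and follow-up".

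On analysis, section 7.1 states: "Longitudinal changes in echocardiographic parameters and HRQoL will be analysed using mixed-effects models to account for repeated measurements within patients". The significance level is 0.05, two-sided. Section 11.2 fixes the comparator: "MR progression will be defined as an increase of at least one MR grade compared with baseline". The appendix grades MR from I to IV, with moderate to severe as Grade III. Section 11.4 makes non-worsening MR severity part of treatment success for conservatively managed patients.

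The protocol does not say which echo is the baseline, gives no reliability for any echo measure, and does not mention regression to the mean.

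**The concern.** A patient is enrolled because a reading reached a threshold. That reading is the stable severity plus the error of the day (reader variation, loading conditions). Among enrolled patients the error at entry is positive on average, because readings below the threshold are absent. Follow-up readings are not filtered in this way, so their mean error is zero. If the qualifying reading is also time 0, the MR-severity measures drop at the next visit with no change in the valve.

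A random patient effect does not remove this, since selection acts on the error of the first reading and not on the patient effect. Stratifying by aetiology or management does not remove it either.

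MR progression is a stated secondary objective (section 2.2). A stable cohort could be reported as improving and a slowly worsening one as stable. Conservatively managed patients would also meet the non-worsening part of treatment success more easily.

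**Working it through.** **Inputs from the protocol.** Entry on one echo (5.7, 8.2); baseline as comparator (11.2); annual follow-up for five years (5.3); two-sided 0.05 (7.1). No sample size or effect size is given, so there is no planned figure to reproduce.

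**Assumptions, because the protocol gives no values.** Test-retest reliability r = 0.70 to 0.95; share of screened echoes that qualify 10 to 50%; n = 100, 300 or 1000; complete data; no deaths or interventions; qualifying echo used as year 0.

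**Step 1: expected fall with no true change.** In SDs of the observed reading, with c the entry cut-off:

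fall = (1 − r) × φ(c) / share

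For a 30% share, c = 0.524 and φ(c)/share = 1.159. At r = 0.80 the fall is 0.20 × 1.159 = 0.232 SD.

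| Share | r = 0.70 | 0.80 | 0.90 | 0.95 |
|---|---|---|---|---|
| 10% | 0.526 | 0.351 | 0.175 | 0.088 |
| 30% | 0.348 | 0.232 | 0.116 | 0.058 |
| 50% | 0.239 | 0.160 | 0.080 | 0.040 |

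**Step 2: effect on the slope.** With visits at years 0 to 5 the mean time is 2.5 and the sum of squares is 17.5, so year 0 has weight −2.5/17.5 = −1/7. An entry reading too high by the fall shifts the slope by −fall/7. For a 30% share and r = 0.70 this is −0.348/7 = −0.050 SD per year; the simulation gave −0.0498.

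**Step 3: rejection of no change when nothing changes.** The test is a t-test on per-patient slopes, years 0 to 5, the balanced-data counterpart of a random-slope mixed model. Without selection it rejected in 4.8% (n = 100) and 4.9% (n = 300) of runs. With selection:

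| n, share | r = 0.70 | 0.80 | 0.90 | 0.95 |
|---|---|---|---|---|
| 300, 10% | 100% | 100% | 100% | 98% |
| 300, 30% | 100% | 100% | 97% | 74% |
| 300, 50% | 99.9% | 95% | 76% | 44% |
| 100, 30% | 97% | 90% | 59% | 34% |

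Across all settings the range is 19% to nearly 100% at n = 100 and 93 to 100% at n = 1000. If only Grade III qualifies (n = 300; 30% at Grade III or above, 10% at Grade IV), the figures are 100%, 98%, 82% and 55%. The slope over years 1 to 5 alone rejects in 3 to 8% of runs, within simulation error of 5%.

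**Step 4: attenuation or masking (30% share, n = 300).** Mean estimated slope, SD per year:

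| True slope | r = 0.70 | 0.80 | 0.90 | 0.95 |
|---|---|---|---|---|
| +0.02 | −0.030 | −0.013 | +0.003 | +0.012 |
| +0.05 | 0.000 | +0.017 | +0.033 | +0.041 |
| +0.10 | +0.050 | +0.067 | +0.083 | +0.092 |

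**Step 5: the grade rule with no true change** (assumed 30% at Grade III or above, 10% at Grade IV; both enter):

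| r | Baseline to year 1: worse / better | Year 1 to year 2: worse / better |
|---|---|---|
| 0.70 | 11.8% / 48.2% | 27.2% / 27.3% |
| 0.80 | 11.5% / 41.2% | 24.1% / 23.9% |
| 0.90 | 9.4% / 30.6% | 18.8% / 18.7% |
| 0.95 | 7.4% / 21.9% | 14.1% / 14.1% |

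The asymmetry disappears once the entry reading is out. The false-progression share, however, about doubles: 24.1/11.5 = 2.1 at r = 0.80. With 5 to 20% qualifying and r from 0.70 to 0.98 it goes from about 5–12% to about 9–30%.

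**Step 6: measures not used for selection.** If their visit error is independent of the MR reading error, rejection stays at 3 to 7%. With an assumed error correlation of 0.3 it runs from 7 to 100%, depending on n, r and share.

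**The case against.** The strongest reply is that the protocol never states the premise. It does not say that the qualifying echo is the baseline, that the baseline value belongs to the outcome vector, or that a no-change hypothesis is tested. Section 5.3 leaves room for a separate study echo, the appendix records a visit date and an echo date separately, and the flow diagram is not shown. Model details of this kind often stand in a statistical analysis plan, which is not at hand. All of this stands as a limit on certainty. It does not dispose of the point: sections 5.2 and 5.4 make a second echo before follow-up unlikely, and section 11.2 itself fixes baseline as the reference for progression.

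A reader might infer that every longitudinal result is biased, because the sentence in 7.1 covers all echo parameters and HRQoL. The documents do not support that. Patients are not selected on LVEF, LVEDD, LAVi or SF-36.

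A reader might also infer that the baseline reading should be dropped throughout. That would discard sound baseline data on remodelling and HRQoL, and it would remove the interval from entry to first follow-up, where the effect of an early intervention on MR lies. Nor is re-referencing the grade rule a clean cure: it balances up against down but raises false progression, as step 5 shows.

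**Conclusion.** The point holds for MR grade, EROA, regurgitant volume, vena contracta and PISA radius, on the probable but unstated premise that the qualifying echo is the baseline. Given that premise, the direction of the bias is certain: towards apparent improvement and away from progression. Its size is not, because it depends on reliability, qualifying share and cohort size, none of which the protocol gives. In the ranges assumed, the false fall is 0.04 to 0.53 SD, and a slope test including the entry reading rejects in 44 to 100% of runs at n = 300.

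It would go too far to say that progression is masked outright. True worsening of 0.02 SD per year is reversed at reliability 0.70 or 0.80, and 0.05 is cancelled at 0.70. At reliability 0.90 or more, 0.05 is only attenuated, and 0.10 was still detected in about 100% of runs at every reliability tried. The simulations also leave out deaths, interventions and missed echoes. The matter concerns a secondary objective; the co-primary endpoints are not touched.

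**What to change.** In section 7.1:
- State which echo is the baseline.
- For the MR-severity measures only, base the conclusion on natural progression, in patients before or without mitral intervention, on the trend from the first follow-up echo onward, with the baseline value as covariate. Report it beside the model from baseline.
- Label the change from baseline to first follow-up as including regression to the mean.
- Keep the baseline in the models for remodelling, HRQoL and change after intervention.

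In section 11.2:
- Keep the proportion referenced to baseline, but report both at least one grade worse and at least one grade better.
- Show the version referenced to the first follow-up echo only as a sensitivity analysis, also in both directions, because its false-progression share is about two to three times higher.

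The cost is wording and one further model; no echo or data item is added. The follow-up-only trend rests on patients with at least two follow-up echoes, hence on survivors, and loses some precision.
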